**Table 1 T1:**
[figure not shown]
Specific components in Hou Gu Mi Xi.

#### Recuperation treatment period (weeks 7 to 52)

2.4.3

All participants will enter the recuperation treatment period at the beginning of week 7. In this period, the doses of HGMX and placebo will remain unchanged (ie, 30 g b.i.d.) for all groups for a 46-week recuperation treatment. Rabeprazole will not be administered to the corresponding groups during this period.

#### Extension period (weeks 53 to 104)

2.4.4

This is an observational period. All the interventions will be stopped, but follow-ups and outcome assessments will continue.

#### Co-interventions

2.4.5

If participants have comorbidities not specified in the exclusion criteria, they will be allowed to receive targeted therapy, such as oral hypoglycemic drugs and insulin for diabetes, hypotensive drugs for hypertension, and antiallergy drugs for asthma.

Medicines that may damage the gastrointestinal tract, such as NSAIDs, theophylline and potassium supplements, and those that have a similar effect as our treatment, such as other PPIs, bismuth, and other Chinese herbal medicines, are prohibited.

### Outcomes

2.5

#### Primary outcomes

2.5.1

1.The total effective rate of PUD treatment will be calculated as (clinical cure + markedly effective + effective)/total number of participants. Efficacy will be assessed by Sakita–Miwa's method.^[22]^ First, ulcer healing status will be classified into 6 categories:A1: the ulcer is round or elliptical, with a thick and white covering in the center; it can be accompanied by errhysis or blood clots and surrounded by obvious swelling, hyperemia, and oedema.A2: the ulcer is covered by yellow or white patches, with no bleeding and less swelling and edema.H1: the ulcer is healing; the coating of the ulcer becomes thin and subsides, hyperemia and edema disappear around the ulcer, and new capillaries appear.H2: the ulcer becomes shallow and small; the surrounding mucosa plica is central to the ulcer.S1: the white coating of the ulcer disappears, and the new ulcer mucosa is red.S2: the new ulcer mucosa changes from red to white.Then, the efficacy will be ranked according to the following 4 levels based on ulcer rehabilitation and recovery:Clinical cure: the ulcer completely heals with or without a scar.Markedly effective: the ulcer heals to grade H2 or improves 2 grades.Effective: the ulcer heals to grade H1 or improves by 1 grade.Noneffective: no efficacy by endoscopic observation.2.The quality of ulcer healing will be classified as follows by histopathological examination using Pan's criteria^[23]^:Good: integral villus and epithelium, many glands, good morphology, many capillaries, and limited inflammatory cell infiltration.Fair: short villus, incomplete or rough epithelium, fewer glands, structural distortion, few capillaries, and moderate inflammatory cell infiltration.Poor: few new epithelial cells, poor epithelium integrity, poor morphology of villus and glands, very few capillaries, and a large number of inflammatory cells.3.The changes in SQD symptoms will be assessed based on the Spleen Qi Deficiency Symptoms Grading and Quantifying Scale (SQD scale) score.^[19]^ This is a modified version of the classic scale that has a total of 15 items to assess 7 main symptoms and 8 secondary symptoms. Four aspects of SQD symptoms will be assessed, including severity, duration per episode, number of attacks per day, and number of affected days per week. The total score of each item is the sum of points for the 4 aspects in all items (items assessing the main symptoms receive double weight). The score ranges from 0 to 283 points, and a higher score indicates worse symptoms (see details in Supplementary file).

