#### Inclusion criteria

2.2.1

1.Diagnosed with GU or DU by endoscopy and ulcer area from 0.3 to 1.0 cm^2^ with no indications of bleeding or perforation.2.Diagnosed with SQD according to the criteria in the Consensus on Integrated Traditional Chinese and Western Medicine, as follows:Main spleen deficiency (SD) symptoms: poor appetite; stomach or abdominal distention; loose stools or diarrhea.Main qi deficiency (QD) symptoms: physical fatigue and weakness; mental fatigue and taciturnity.Secondary symptoms: loss of taste or hypodipsia; stomach or abdominal pain; stomach tightness; nausea or vomiting; abnormal bowel sounds; lean or puffiness; sallow complexion; powerless defecation; facial or limb oedema.Tongue symptoms: pale, swollen, or scalloped tongue with a thin, white coating.Patients will be diagnosed with SQD if they meet: 2 main SD symptoms + 2 main QD symptoms; 2 main SD symptoms + 1 main QD symptom + 1 tongue symptom; or 1 main SD symptom + 1 main QD symptom + 2 secondary symptoms + 1 tongue symptom.3.Aged from 18 to 70 years.

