
#### Secondary outcomes

2.5.2

1.Ulcer area (cm^2^) measured by endoscopy.2.Recurrence of PUD after standard and maintenance treatment, as measured by endoscopy.3.Incidence of bleeding and perforation after standard and maintenance treatment, as measured by endoscopy.4.*H pylori* eradication rate defined as a change in delta over baseline (DOB) value to <4 in the 13C-urea breath test during follow-up for *H pylori*-positive patients.5.Gastric function evidenced by analysis of gastrin-17 (pg/mL), pepsinogen I (ng/mL), and pepsinogen II (ng/mL).6.Changes in body weight (kilogram) and body mass index (kilogram per meter square).

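### The total effective rate rule can count an ulcer that never improved, or one that healed and recurred, as a treatment success

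*Protocol article*

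**What the plan says.** Section 2.5.1 of the protocol article defines the first primary outcome, the total effective rate, as "calculated as (clinical cure + markedly effective + effective)/total number of participants". Ulcers are staged A1, A2, H1, H2, S1 or S2, and the stages are then turned into four efficacy levels. Below complete healing there are two success levels:

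- "Markedly effective: the ulcer heals to grade H2 or improves 2 grades"
- Effective: "the ulcer heals to grade H1 or improves by 1 grade"

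The failure level has no grade criterion: "Noneffective: no efficacy by endoscopic observation".

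Five other parts of the article bear on how this rule works.

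- **Eligibility (2.2.1, 2.2.2).** The ulcer criterion is "Diagnosed with GU or DU by endoscopy and ulcer area from 0.3 to 1.0" cm², without bleeding or perforation. No stage is required at entry. The exclusions remove Forrest I, IIa and IIb ulcers and positive occult blood, but not H1 or H2 ulcers.
- **Recurrence (2.5.2).** It is a separate secondary outcome: "Recurrence of PUD after standard and maintenance treatment, as measured by endoscopy".
- **Visits (2.6).** Follow-up gastroscopy is at weeks 12, 26, 52 and 104.
- **Withdrawal and missing data (2.7, 2.10).** A patient with an acute recurrent ulcer is withdrawn. Missing primary outcome data are filled by LOCF.
- **Discussion (3).** The assessments after week 12 are meant to show the long-term effect of Hou Gu Mi Xi (HGMX) on outcomes that include the total effective rate.

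**The concern.** Each of the two partial success levels can be met in either of two ways: by standing at a given grade, or by gaining grades. Standing at a grade is not evidence of a treatment effect when nothing prevents a patient from entering at that grade. A gain over entry does not show a lasting effect when the ulcer has healed and come back in between.

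The total effective rate is the outcome on which the trial was sized (2.9). Successes that do not depend on treatment raise both arms and shrink the difference between them. Relapses scored as successes have a second consequence. The introduction hypothesises that HGMX reduces recurrence, and the later total effective rate would be partly blind to that, whether HGMX succeeds or fails in it.

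**Working it through.** **1. The plan's own sample size.** Inputs from 2.9: 85% versus 65%, α = 0.05 (taken as two-sided, which the text does not state), power 80%, drop-out 15%. With the common-variance formula n = 2·p̄(1−p̄)·(z₀.₉₇₅ + z₀.₈₀)²/d², p̄ = 0.75 and d = 0.20:

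- n = 0.375 × 7.849/0.04 = 73.6, so 74 per group
- 74/0.85 = 87.1, so 88 per group and 352 in all

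This is within two patients per group of the stated 90 (360). The sample size is not the problem.

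**2. The rule applied literally.** S1 and S2 are taken as complete healing, and entry is taken as the reference. For later grades below healing:

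| Entry | Later A1 | Later A2 | Later H1 | Later H2 |
|---|---|---|---|---|
| A1 | noneffective | effective | markedly effective | markedly effective |
| A2 | noneffective | noneffective | effective | markedly effective |
| H1 | noneffective | noneffective | **effective** | markedly effective |
| H2 | noneffective | noneffective | **effective** | **markedly effective** |

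The three cells in bold are successes without improvement. H1 to H1 and H2 to H2 are unchanged; H2 to H1 is a worsening.

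**3. What the absolute limbs add.** A2 to H1 is already a gain of one grade, A1 to H1 of two, and H1 to H2 of one. All are successes on the relative limb alone. For the total rate, the absolute limbs therefore add only the three bold cells.

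**4. Relapse.** Take a patient who enters at A1, is healed at week 12 and has an ulcer again at a later gastroscopy. Against entry, a recurrent ulcer at A2 has gained one grade (effective), and one at H1 or H2 has gained at least two (markedly effective). Only a recurrence at A1 fails. For a patient who entered at A2, a recurrence at H1 or H2 succeeds in the same way. None of this depends on how the absolute limb is read; it depends only on entry being the reference. Separately, a patient withdrawn for acute recurrence may have a healed ulcer as the last graded observation, and LOCF then carries that success forward.

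**5. Illustration of size.** Assume that a share h of patients in both arms are automatic successes and that 85% versus 65% holds in the rest. The rates are h + (1−h)·0.85 and h + (1−h)·0.65, so the difference is (1−h)·0.20. Power is Φ[(d − 1.96·√(2p̄(1−p̄)/n))/√((p₁q₁ + p₂q₂)/n)], with q = 1 − p. The pooled comparison has 180 × 0.85 = 153 evaluable patients per side.

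| h | HGMX | Placebo | Difference | Pooled power |
|---|---|---|---|---|
| 0 | 85.0% | 65.0% | 20 points | 98% |
| 0.1 | 86.5% | 68.5% | 18 points | 97% |
| 0.2 | 88.0% | 72.0% | 16 points | 94% |
| 0.3 | 89.5% | 75.5% | 14 points | 90% |

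For a comparison of single groups (90 × 0.85 = 76.5, taken as 76 evaluable), power would fall from 82% at h = 0 to 76%, 70% and 62%. That is not the contrast for which 2.9 states its rates. The values of h are assumptions. They illustrate the unchanged-ulcer part only, as the article gives no relapse rate.

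**The case against.** **Change was probably intended.** The verb *heals* and the failure label both point to change. An ulcer at H1 before and after has not healed to anything, and an assessor could fairly call it noneffective. The H2 limb also has a purpose on that reading: it lifts H1 to H2, a one-grade gain, from effective to markedly effective. This stands as evidence of intent, so a reader should not infer that the sponsor meant unchanged ulcers to succeed. But that lift does not change the total rate, and the failure level has no grade criterion to settle the matter. Two assessors could score the same unchanged ulcer differently.

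**Few patients may be affected.** Treatment for peptic ulcer within three months is an exclusion (2.2.2), so ulcers already healing under therapy should be uncommon at entry. Many H-stage entrants would heal completely and succeed under any rule. This stands, and it is why no size is claimed.

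**The trial is not shown to be underpowered.** A reader might infer that it is from the diluted differences or the single-group powers. The documents do not support this. Section 2.9 gives its rates for the two HGMX groups against the two placebo groups, and pooled power stays at 90% or more in the range shown. The rates of 85% and 65% are also stated for the total effective rate itself, so they may already include automatic successes. In that case there is no loss against the plan.

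**Relapse is reported elsewhere.** Recurrence is a secondary outcome, so it would not go unseen. The reference examination is not named, so comparison with entry is the natural reading but not a stated rule. Both points stand. They do not make the later total effective rate interpretable as a long-term effect.

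**The article is condensed.** Scoring detail may sit in a fuller document. But the article sets out the rule level by level, and the difficulty lies in what it states.

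**Conclusion.** The concern holds as a defect in a stated primary outcome rule.

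- **Unchanged ulcers.** This part depends on a literal reading and on H1 or H2 ulcers being enrolled. The criteria allow that, but the share is not given.
- **Recurrent ulcers.** This part is firmer. Nothing in 2.5.1 makes a recurrence a failure. With entry as the reference, a recurrence at a better grade than entry is a success, and withdrawal followed by LOCF can have the same result.

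The size is unknown. On the assumed 10-30% of automatic successes, the difference falls from 20 points to 18-14 and pooled power from 98% to 97-90%, above the 80% target. The case for change rests on the meaning of the later total effective rate and on consistent scoring, not on a shortfall in power.

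**What to change.** In 2.5.1:

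1. Define success as complete healing, or a grade at least one better than at the patient's own baseline endoscopy.
2. Score an unchanged or worse H1 or H2 ulcer as noneffective.
3. Score an ulcer that has recurred after documented healing as noneffective at the visit where it is seen. Score a withdrawal for acute recurrence in the same way, rather than by LOCF.

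Whether the failure persists if the ulcer heals again is for the sponsor to decide and write down before unblinding. The change concerns scoring only and leaves treatment and withdrawal rules as they are.

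The cost is a few sentences, since the gastroscopies and grades are already planned. The effective rate may be lower in both arms. For example, if the automatic successes in the illustration, properly scored, succeeded at the same 85% and 65% as the rest, the HGMX rate would fall by 1.5-4.5 points (86.5 − 85 to 89.5 − 85). The placebo rate would fall by 3.5-10.5 points (68.5 − 65 to 75.5 − 65).

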#### Exclusion criteria

2.2.2

1.Complex peptic ulcer (ie, simultaneous GU and DU).2.History of ulcer complications (eg, bleeding, perforation, pyloric stenosis, and precancerous lesions).3.Indications of ulcer complications, including bleeding and perforation (Forrest stage I, IIa or IIb; positive stool occult blood; or ulcer area >1 cm^2^).4.History of use of NSAIDs, theophylline, oral antibiotics, potassium supplements, or any intervention for PUD within the last 3 months.5.Pregnant, breastfeeding, or planning to become pregnant within 2 years.6.Allergic to any trial interventions.7.Impaired liver or renal function, indicated by total bilirubin >35 μmol/L, alanine transaminase >2× upper limit of normal (ULN), aspartate aminotransferase >2× ULN, or serum creatinine >ULN.8.Other severe diseases (e.g., severe mental disorders and cancer).9.Unwilling to provide personal information.

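### The printed healing-quality grades all rest on the villus and do not fit biopsies from the gastric ulcers that the trial also enrols

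*Protocol article*

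**What the plan says.** Section 2.2.1 of the Protocol article opens its first criterion with "Diagnosed with GU or DU by endoscopy". Section 2.2.2 excludes "Complex peptic ulcer (ie, simultaneous GU and DU"), so each patient has one ulcer site.

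Section 2.5.1 makes histological quality of ulcer healing the second of three primary outcomes, graded by cited criteria that the article prints as three levels:

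- The top level is "Good: integral villus and epithelium, many glands, good morphology, many capillaries, and limited inflammatory cell infiltration".
- The middle level is "Fair: short villus, incomplete or rough epithelium, fewer glands, structural distortion, few capillaries, and moderate inflammatory cell infiltration".
- The bottom level includes "poor morphology of villus and glands, very few capillaries, and a large number of inflammatory cells".

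No gastric version of the levels is given, and nothing is said about a biopsy from mucosa without villi.

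Histology is read at weeks 12 and 26 (2.6). The Discussion makes healing quality the focus of the week-12 assessment of HGMX and rabeprazole. Section 2.10 compares categorical outcomes by Pearson chi-square and uses ulcer type only to define a subgroup analysis. Section 2.3 describes block randomisation and mentions no stratification by ulcer type.

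**The concern.** Villi are a feature of duodenal mucosa; normal gastric mucosa has surface epithelium, pits and glands. That is basic anatomy, not a statement in the protocol, and it is the only outside premise needed. A scale whose every level is partly defined by the villus therefore describes one of the two enrolled ulcer types and not the other.

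This is not a complaint about detail left to a fuller document. The three definitions are printed, and the printed wording does not fit part of the trial population.

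What is at stake is how well a primary outcome measures healing. If the grade depends partly on where the ulcer was, it is noisier as a measure of healing, an effect of HGMX in GU patients may be compressed, and a difference between GU and DU in healing quality or in effect size cannot be separated from a difference in how the scale works at each site.

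**Working it through.** The protocol states no figure that this point disputes, so there is nothing to reproduce. The check is a reading of the text, followed by an illustration of scale.

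**Reading the text.** Take a GU patient whose mucosa is fully restored: complete epithelium, many glands, many capillaries, little inflammation, no villi.

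1. *Villus item applied literally.* Good asks for an integral villus, which is absent. Fair asks for a short villus, also absent. Poor refers to poor villus morphology, which cannot be judged. No level describes this biopsy.
2. *Villus item ignored for gastric biopsies.* The patient can be graded Good on the other features. GU is then graded on a shorter list than DU, and the two sets of grades are pooled as one outcome.

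Either way, the meaning of a grade depends on ulcer site.

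**Scale of the dilution (illustration).** Inputs:

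- Patients per HGMX margin: two groups of 90 = 180 (2.9). With the 15% drop-out of 2.9, 180 × 0.85 = 153 analysed per side.
- Two-sided α = 0.05. The value 0.05 is from 2.9; two-sided is an assumption.
- Good rate where attainable: 60% with HGMX, 40% with placebo (assumed).
- GU share g, the same in both arms: not given; taken as 0% to 70% (assumed).
- Good unattainable in GU. This is the extreme literal case.

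The overall rates are p₁ = 0.60(1 − g) and p₂ = 0.40(1 − g), so the difference is 0.20(1 − g). With p̄ the mean of p₁ and p₂,

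power = Φ{[(p₁ − p₂)√n − 1.96√(2p̄(1 − p̄))] / √(p₁(1 − p₁) + p₂(1 − p₂))}.

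The pooled column uses n = 153. The last column uses the DU patients alone, n = 153(1 − g) at 60% v 40%. It approximates a comparison stratified by ulcer type when GU carries no information on Good.

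| GU share | Good, HGMX v placebo | Difference | Power, pooled | Power, DU patients only |
|---|---|---|---|---|
| 0% | 60% v 40% | 20 points | 94% | 94% |
| 20% | 48% v 32% | 16 points | 82% | 88% |
| 30% | 42% v 28% | 14 points | 73% | 84% |
| 50% | 30% v 20% | 10 points | 52% | 70% |
| 70% | 18% v 12% | 6 points | 31% | 48% |

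On these assumptions stratification recovers part of the loss. The rest returns only if gastric biopsies can be graded properly.

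**Chance imbalance in site.** At an assumed 40% GU and 180 per side, the standard deviation of the between-arm difference in GU share is √(2 × 0.40 × 0.60 / 180) = 5.2 points. An imbalance of 10 points or more is 10/5.2 ≈ 1.9 standard deviations, about a 5% chance. The ordinary sampling variance of a two-group test already allows for this, so type I error is not inflated.

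**The case against.** **The cited criteria are not at hand.** The article prints a short English version. The word villus may translate a broader term for surface structures, or the source may have gastric descriptors. A reading guide may also sit in the full protocol or in the procedures on which investigators are trained (2.8). This stands as a limit on certainty. It does not rescue the printed text, and if the source has a gastric descriptor the remedy is simply to state it.

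**The features may be weighed as a whole.** The article does not say how the listed features combine. A pathologist grading on the overall picture might well call a restored gastric biopsy Good. That too stands: the total block on Good is the extreme case, and the power figures above mark an outer bound. But overall judgement at one site and villus-based judgement at the other is the second reading in the working, with its own pooling problem.

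**Stronger readings that the documents do not support:**

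- *That a site imbalance between arms would create a false treatment effect.* Site is balanced in expectation, and a large chance imbalance is uncommon.
- *That the planned subgroup analysis is worthless.* It compares arms within GU and within DU, and both arms in a stratum are graded on the same terms. Those comparisons remain valid, though the GU effect may be compressed. What is hard to interpret is a contrast between the two sites.
- *That hospitals will grade differently.* The article does not say whether slides are read locally or centrally.

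**Conclusion.** The point holds as a mismatch between a printed primary-outcome definition and the enrolled population. It rests on two facts in the text (a villus item in every grade, and both ulcer sites enrolled) and on one fact of anatomy.

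The consequence is loss of sensitivity and of interpretability across sites. It is not bias between HGMX and placebo. Its size cannot be fixed from the documents, because the GU share, the Good rates and the way the features combine are not given. It runs from little, if gastric biopsies are sensibly graded on the other features, up to the dilution tabulated above. The sample size in 2.9 rests on the total effective rate and is untouched.

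The change should be made, since the outcome is primary and is the stated focus at week 12.

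**What to change.** In 2.5.1, before unblinding, state how the cited criteria apply to gastric biopsies. Use the villus item for duodenal biopsies only. Grade gastric biopsies on the remaining listed elements (epithelium, glands, capillaries, inflammatory cells), or on the source's own gastric descriptor if it has one. Apply the rule to all slides, including any already read.

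In 2.10, make the main between-arm comparison of this outcome stratified by or adjusted for ulcer type, for example by a stratified Cochran–Mantel–Haenszel test or an ordinal regression with ulcer type as a covariate. Ulcer type is already known from the eligibility endoscopy.

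The biopsies, visits and sample size stay as they are. The cost is a documented clarification of, or small departure from, the cited criteria. Recruitment began in July 2017 and ethics committees at 11 hospitals approved the protocol, so an amendment is likely to be needed and some gastric slides may have to be re-graded.

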
#### Secondary outcomes

2.5.2

1.Ulcer area (cm^2^) measured by endoscopy.2.Recurrence of PUD after standard and maintenance treatment, as measured by endoscopy.3.Incidence of bleeding and perforation after standard and maintenance treatment, as measured by endoscopy.4.*H pylori* eradication rate defined as a change in delta over baseline (DOB) value to <4 in the 13C-urea breath test during follow-up for *H pylori*-positive patients.5.Gastric function evidenced by analysis of gastrin-17 (pg/mL), pepsinogen I (ng/mL), and pepsinogen II (ng/mL).6.Changes in body weight (kilogram) and body mass index (kilogram per meter square).

